**11. Statistical design**

**11.1 Experimental design**

**It is a therapeutic trial of equivalence, with two parallel groups of which the main criterion is the rate of clinical cure at the end of treatment (D21).**

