**11.2 Number of patients**

The calculation of the number of patients was carried out under the following conditions: the equivalence is accepted up to a maximum variation of 10% between clinical cure rates. The rate of successful treatment for the usual duration of antibiotic therapy (15 days) is between 80 and 90%.

Patients are randomized after the result of the BAL: it is estimated that 20% of patients pre-included may not be included permanently. This produces a risk equal to 0.20. The number of subjects to be included must be a minimum of 275 and maximum of 350 for the initial value of the rate of cure and the risk (chosen, as indicated in the table below):

| %  cured |  |  | n/group | N pre included | Total included |
| --- | --- | --- | --- | --- | --- |
| 0.90 | 0.05 | 0.20 | 110 | 275 | 220 |
| 0.85 | 0.10 | 0.20 | 110 | 275 | 220 |
| 0.80 | 0.10 | 0.20 | 140 | 350 | 280 |

The number of patients selected for the study is 350.

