**11.3 Study duration**

With the recruitment of investigators centres, we estimate the total number of patients included per year to be 120. Therefore, a total study duration of 3 years is estimated in order to recruit the required number of patients who will additionally be followed for 21 days. Every 4 months, a balance sheet of the inclusions will be sent to all investigators centres. To be accepted in the final analysis, each centre must recruit at least 6 patients.

- 1. **Statistical analysis**
- Patients excluded from the analysis include those whose bacteriological samples collected during pre-inlusion do not respond to the criteria laid down.
- Analysis: Non-excluded patients will be analysed by the treatment defined by the drawing of lots (intention to treat). Comparatability of the 2 groups will be performed on the main characteristics and prognostic factors with traditional tests: test t Student for quantitative variables and test of Chi 2 qualitative variables. For the main criterion, the equivalence will be judged by the confidence interval of the odds ratio of the percentage risk (test of decentralized Chi 2).

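### The margin is a 10-point difference in cure rates, but the decision sentence uses an odds-ratio interval with no limit, and the two are not reconciled

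*Protocol*

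**What the plan says.** Section 11.1 of the protocol describes the design: "It is a therapeutic trial of equivalence, with two parallel groups of which the main criterion is the rate of clinical cure", assessed at D21. Section 3.1 likewise states the primary objective as equivalence of 8 and 15 days.

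Section 11.2 gives the margin: "the equivalence is accepted up to a maximum variation of 10% between clinical cure rates". It also gives the reference rate: "The rate of successful treatment for the usual duration of antibiotic therapy (15 days) is between 80 and 90" percent. The row behind the selected size reads "0.80 | 0.10 | 0.20 | 140 | 350 | 280", that is, 140 per group, 280 included and 350 pre-included.

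The statistical analysis paragraph that follows section 11.3 gives the decision rule for the primary endpoint: "the equivalence will be judged by the confidence interval of the odds ratio of the percentage risk (test of decentralized Chi 2", where the bracket closes. The protocol states no odds-ratio limit, no conversion of the 10% into an odds ratio, no reference rate for such a conversion and no confidence level.

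**The concern.** The margin is stated and sized on one scale, and the decision is worded on another. A 10-point difference does not correspond to a single odds ratio. The matching odds ratio depends on the cure rate in the 15-day arm, which the protocol gives only as a range. Whoever runs the analysis therefore has to choose a conversion, and that choice changes both the loss of efficacy that is tolerated and the chance of success. This is the only decision rule stated for the primary objective, and the trial is open, so the rule should not be left to interpretation.

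**Working it through.** **Inputs.** Margin 10% between cure rates; reference rate 0.80 to 0.90; table rows (0.90, 0.05, 0.20, 110), (0.85, 0.10, 0.20, 110) and (0.80, 0.10, 0.20, 140), all from section 11.2. The column symbols are not legible in the text at hand, so I assume that the second column is alpha and the third is beta (power 0.80). Sidedness is not stated. Equal allocation follows from 2 × 110 = 220 and 2 × 140 = 280.

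**Step 1: which scale was the trial sized on?** Take an absolute margin of 0.10, a true difference of zero and one-sided alpha:

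n per group = 2p(1−p)(z₁₋α + z₁₋β)² / 0.10²

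- p = 0.90, alpha 0.05: 0.18 × (1.645 + 0.842)² / 0.01 → 112 (stated 110)
- p = 0.85, alpha 0.10: 0.255 × (1.282 + 0.842)² / 0.01 → 115 (stated 110)
- p = 0.80, alpha 0.10: 0.32 × (1.282 + 0.842)² / 0.01 → 145 (stated 140)

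Using the variance under a null shifted by 10 points (rates p + 0.05 and p − 0.05) gives 109.2, 113.6 and 142.9. At the stated sizes, power by the simple formula is 0.796, 0.787 and 0.791. The pre-inclusion figures are exact: 220/0.8 = 275 and 280/0.8 = 350. A relative 10% margin gives 138, 160 and 226 per group, and halving alpha gives 142, 158 and 198; neither fits. The margin is therefore an absolute 10 points, with alpha used one-sided.

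**Step 2: the same margin as an odds ratio.** With OR = [q/(1−q)] / [p/(1−p)] and q = p − 0.10:

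- p = 0.80: (0.70/0.30)/(0.80/0.20) = 0.583
- p = 0.85: (0.75/0.25)/(0.85/0.15) = 0.529
- p = 0.90: (0.80/0.20)/(0.90/0.10) = 0.444

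**Step 3: loss tolerated if one odds-ratio limit is fixed.** With o = OR × p/(1−p), the loss is p − o/(1+o), in points:

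| OR limit | 80% cure | 85% cure | 90% cure |
|---|---|---|---|
| 0.583 | 10.0 | 8.2 | 6.0 |
| 0.529 | 12.1 | 10.0 | 7.3 |
| 0.444 | 16.0 | 13.4 | 10.0 |

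**Step 4: power at 140 per group**, p = 0.80 in both arms, one-sided 0.10.

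- Difference scale: SE = √(2 × 0.16/140) = 0.0478. Lower limit: Φ(0.10/0.0478 − 1.282) = 0.79. Both limits: 2 × 0.791 − 1 = 0.58.
- Log odds ratio: SE = √(2/(140 × 0.16)) = 0.299. Limit 0.583: Φ(0.539/0.299 − 1.282) = 0.70. Limits 0.529 and 0.444 give 0.80 and 0.92.

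**Step 5: can the conclusion change?** Two illustrative results, 140 per arm, Wald intervals, one-sided 10% lower limits:

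- 112 cured (15-day) against 107 (8-day): the difference is −3.6 points with lower limit −9.9, which meets the margin. The odds ratio has lower limit 0.559, which fails 0.583 and passes 0.529 and 0.444.
- 112 against 104: the difference is −5.7 points with lower limit −12.1, which breaches the margin. The odds ratio has lower limit 0.500, which still passes 0.444.

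**The case against.** A reader might infer that the stated margin is simply not what will be tested. The document does not support that as a fact. The bracketed chi-square test may mean a non-central or shifted-null test, which can be set against a 10-point difference, and the shifted-null calculation comes close to the tabled sizes. An odds ratio of a percentage risk is not a standard quantity, and the English is visibly translated, so the term may be a slip. What stands is narrower: on that reading the sentence names two decision quantities and does not say which decides.

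A missing numerical limit and confidence level could also be left to an SAP that is not shown, and if a limit were fixed there before the data are seen, the conclusion could not depend on a later choice. That is fair. Their absence alone would be no finding. An SAP limit would not remove the disagreement between two sections of the protocol.

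The 16.0-point figure pairs a limit derived at 90% with a true rate of 80%. The selected size comes from the 80% row, and with that row's limit of 0.583 the tolerated loss within the stated range is never above 10.0 points, so the odds-ratio rule would be stricter. This is correct, but the protocol does not say that this limit applies.

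One might also point out that a 10-point gain from 90% has an infinite odds ratio. That is only a boundary effect, since it means 100% cure. It says nothing about the lower limit, and no weight is placed on it here.

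**Conclusion.** The concern holds in this form: the margin and the size are set on the absolute difference in D21 cure rates, the decision sentence is worded on an odds ratio without a limit, and the protocol does not reconcile them. Across its own 80 to 90% range, the odds-ratio equivalent of a 10-point loss runs from 0.583 to 0.444, and a fixed limit from that span tolerates 6.0 to 16.0 points. At the selected size, a limit of 0.583 costs about 9 points of power (0.70 against 0.79). The figures rest on reading the table's second and third columns as alpha and beta, alpha one-sided, equal allocation, equal true cure rates and normal approximations. It cannot be concluded that the 10-point margin will certainly go untested, because the bracketed test leaves that open.

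**What to change.** Replace the decision sentence with wording such as:

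> The primary analysis is the difference in D21 clinical cure rates (8-day minus 15-day) with its confidence interval. Equivalence is accepted if the whole interval lies between −10 and +10 percentage points. The odds ratio is reported descriptively.

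Keeping both limits agrees with sections 3.1 and 11.1. State the interval level and sidedness outright. Referring to the sample-size alpha is not enough, because the table shows both 0.05 and 0.10 and gives no sidedness. The selected row fits one-sided 0.10 per limit, which is a two-sided 80% interval (1 − 2 × 0.10), if the second column is alpha.

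Restate the power at 140 per group and 80% cure: about 0.79 for the lower limit alone and about 0.58 if both limits must be met. With one-sided 0.05 per limit, these become about 0.67 and 0.34.

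The cost is one sentence and a less favourable stated power. The change itself needs no extra patients or data. Restoring 80% power for both limits (about 211 per group at one-sided 0.10) would be a separate sizing decision.

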**7.2.1 Failure ;**

- Death for what ever reason during the protocol

- Initial clinical worsening judged after D3 of treatment:

septic shock (Appendix IV) or "sepsis syndrome" (Score of organ failure related to sepsis: SOFA Appendix V) without another documented infection - increase in the score of organ failure (increase in SOFA score by 2 points or more) with identification of the same microorganism at a new BAL

- Persistence or increase of all signs of pulmonary infection after D3 of treatment:

- temperature > 38.5° or < 36 °

- > 12000 WBC / mm3 or < 5000 / mm3

- purulent bronchial secretions

- absence of pulmonary radiological improvement and persistence of the original microorganism in the BAL

- A need to change the initial antibiotic for treatment intolerance (Appendix VI)

If failure is diagnosed, regardless of the day (After D3 of treatment), the patient is assessed as failure in the final evaluation at D21.

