**8.3 Randomisation**

Is carried out in the final inclusion. It will be performed by the main investigator centre using a pre-defined centre randomization table. The assigned treatment arm is communicated by fax between 8 a.m. and 12 p.m., Monday to Friday and at the latest by D5.

1. **Methodology**

- **Pre-inclusion**
- verification of the criteria for inclusion (except bacteriological data) and exclusion
- realization of the BAL
- realization of 3 blood cultures
- simplified acute physiologic score: SAPSIIS II (Appendix VIII)(Appendix IX) Mc Cabbe score - score of organ failure (ODIN: Appendix X)
- -score of organ failure related to sepsis (SOFA: Appendix V)
- **Inclusion**
- verification of the bacteriological criteria for inclusion.
- **D0 of treatment**
- SAPS II (Appendix VIII) score
- score of organ failure (ODIN: Appendix X)
- score of organ failure related to sepsis (SOFA: Appendix V)
- **D1 of treatment**
- SAPS II (Appendix VIII) score
- score of organ failure (ODIN: Appendix X)
- score of organl failure related to sepsis (SOFA: Appendix V)
- rectal swabs
- **D4 of treatment**
- **decrease of dosages of beta-lactam - interim evaluation**

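### The primary comparison is valid but ignores severity scores recorded before randomisation; a standardised difference in cure rates would use them, with a gain that depends on how prognostic they are

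*Protocol*

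**What the plan says.** The statistical analysis paragraph after section 11.3 of the protocol analyses patients by randomised arm and decides the main criterion in one sentence: "the equivalence will be judged by the confidence interval of the odds ratio of the percentage risk", by a non-central chi-square test. No covariate is named. Baseline prognostic data have one stated use: "Comparatability of the 2 groups will be performed on the main characteristics and prognostic factors", by t and chi-square tests. Nothing is said to follow from those tests.

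The methodology list after section 8.3 schedules the severity scores at pre-inclusion: "simplified acute physiologic score: SAPSIIS II (Appendix VIII)(Appendix IX) Mc Cabbe score - score of organ failure (ODIN: Appendix X"), followed by SOFA. Section 8.1 places pre-inclusion on the day of the lavage. Sections 8.3 and 11.2 place randomisation after the lavage result. All four scores therefore precede allocation.

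The outcome is clinical cure at D21 (section 11.1). The first item in the failure list of section 7.2.1 is "Death for what ever reason during the protocol". Section 11.2 sets the equivalence margin at 10 percentage points between cure rates.

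**The concern.** Equivalence is decided by the width and position of a confidence interval, so any variance that baseline data can remove bears directly on the chance of a conclusive result. The protocol collects four measures of severity or underlying disease in every patient before allocation. Appendix IX itself describes the McCabe class as separating groups with different prognosis. Because death from any cause is a failure, such measures can be expected to be associated with D21 cure. The plan uses them to describe the groups and leaves them out of the estimate.

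At stake is a moderate amount of power, plus protection of the reported difference against a chance imbalance in severity.

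**Working it through.** **Inputs from section 11.2.** Cure rate 0.80, 140 per group, 280 included, 350 pre-included, margin 0.10. The table's header symbols are lost. Its values 0.10 and 0.20 are read as alpha and beta, with 1:1 allocation assumed from the single n/group column.

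**Step 1: reproduce the plan's figure.** Non-inferiority form, unpooled variance, no true difference:

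- n per group = 2 × 0.8 × 0.2 × (1.2816 + 0.8416)² / 0.10² = 144.3, rounded up to 145, against 140 stated.
- SE at 140 per group = √(2 × 0.8 × 0.2 / 140) = 0.0478.
- Power = Φ(0.10 / 0.0478 − 1.2816) = 0.791.
- Pre-included = 280 / 0.8 = 350, as stated.

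The other two rows give power 0.796 and 0.787 in the same way. The design is therefore a one-sided, unadjusted comparison of cure rates with power close to 80%.

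**Step 2: adjusted, standardised risk difference.** The documents give no figure for R², the share of outcome variance that the scores explain, so it is varied. SE = √(2 × 0.8 × 0.2 × (1 − R²) / 140), with power as in step 1. The gain in effective sample size is 1/(1 − R²) − 1.

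| R² (assumed) | SE | One-sided power | Gain in effective sample size |
|---|---|---|---|
| 0 | 0.0478 | 0.791 | 0 |
| 0.05 | 0.0466 | 0.806 | 5% |
| 0.10 | 0.0454 | 0.822 | 11% |
| 0.20 | 0.0428 | 0.855 | 25% |

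If both interval limits had to lie within 10 points, power with no true difference would be 2 × (one-sided power) − 1: 0.58 at R² 0, 0.64 at 0.10 and 0.71 at 0.20.

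**Step 3: simulation, with the odds-ratio scale alongside.** 4,000 trials per setting, 140 per group, cure 0.80, no true difference, one-sided 0.10. The odds-ratio margin is an assumption: 70% against 80% cure gives (0.70/0.30)/(0.80/0.20) = 0.58.

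| Score AUC | R² | Variance ratio, standardised v crude difference | SE of log OR, crude → conditional | Power against OR 0.58, crude → conditional |
|---|---|---|---|---|
| 0.61 | 0.025 | 0.97 | 0.302 → 0.308 | 0.695 → 0.682 |
| 0.68 | 0.07 | 0.93 | 0.303 → 0.316 | 0.699 → 0.675 |
| 0.75 | 0.13 | 0.87 | 0.302 → 0.327 | 0.693 → 0.644 |
| 0.81 | 0.22 | 0.80 | 0.302 → 0.345 | 0.692 → 0.612 |

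The variance ratios agree with 1 − R². On the log odds-ratio scale the conditional standard error rises by 2% to 14%. With no true difference and a fixed margin, nothing offsets that increase.

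**Step 4: how many covariates the data can carry.** Expected failures among 280 patients are 280 × 0.20 = 56 at 80% cure and 280 × 0.10 = 28 at 90% cure. Arm, SAPS II and the three-level McCabe class use 1 + 1 + 2 = 4 coefficients. That is 14 failures per coefficient at 80% cure and 7 at 90%.

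**The case against.** The strongest reply is that nothing here is an error. An unadjusted comparison of randomised groups is valid, covariates are often left to a statistical analysis plan, and that plan is not shown. The validity point stands in full. The second point stands in part: a later plan may add covariates, but the protocol does name the effect measure, the test and the use of prognostic factors, so the choice can be discussed as written.

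A reader might infer that adjustment would narrow the interval the protocol names. It would not if the adjustment were an ordinary logistic model: step 3 shows the conditional odds-ratio interval widening, and the quantity estimated changes as well. The gain comes from a standardised estimate. Moving to a difference in cure rates also removes the gap between an odds-ratio interval and a margin set on rates, but that gap is a separate matter.

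A reader might also infer a definite loss in patients. The documents do not support one, because they do not say how well the scores predict D21 cure. Death is only one route to failure: section 7.2.1 also counts persistent pulmonary signs and treatment intolerance, and cure depends on secretions, radiology and oxygenation. In the simulation, R² values of 0.13 and 0.22 needed AUCs of 0.75 and 0.81. If the scores do not predict cure, the gain is nil.

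Finally, not every scheduled score is safe to use. D0 is the start of treatment (section 5.2), treatment may wait for the lavage result (section 5.1), and randomisation follows that same result. D0 and D1 scores can therefore fall after allocation. The scheduled arms do not diverge until D9, so any distortion should be small, but only pre-inclusion values are certain to be baseline.

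**Conclusion.** The point holds as a missed efficiency, not as a flaw in validity. The primary comparison names no covariate, although four plausibly prognostic scores are in hand before randomisation. Relative to a standardised risk difference, the cost is 0 to about 6 points of one-sided power (0.791 against 0.791 to 0.855) at 140 per group, 80% cure, alpha 0.10 and a 10-point margin. This rests on an assumed R² of 0 to 0.20 and on reading the sample-size table as one-sided. At R² 0.05 the gain is 1.5 points; at 0.10 it is about 3. The documents support neither bias in the crude analysis nor any narrowing of a conditional odds-ratio interval.

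**What to change.** In the statistical analysis paragraph, state that:

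- the primary estimate is the difference in D21 cure rates between arms, standardised over all analysed patients from a logistic model with arm and one or two pre-inclusion scores (for example SAPS II and McCabe class), not D0 or D1 values;
- its confidence interval is judged against the 10-point margin of section 11.2;
- the crude difference is reported beside it.

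If an odds ratio is still wanted, the same standardised rates give a marginal one. It should be secondary, because the margin is not on that scale.

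The cost is small but not nil. No extra patients or measurements are needed. The effect measure changes from the odds ratio to a difference, which is more than a change of wording. A rule for missing scores is required. The covariate list must stay short, since only about 28 to 56 failures are expected among 280 patients and the severity scores overlap.

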**12. Presentation of the results**

Communication will be presented to the « l’Agence Nationale d’Evaluation des Médicaments » to various scientific societies, society of critical care of French language (SRLF), French society of anesthesia and surgical critical care (SFAR), international conferences and submitted for publication.

**APPENDIX**

**Appendix I : Radiologic Score**

By quadrant: 0: normal

1: interstitial infiltrate

2: non-confluent cellular infiltrate

3: condensation

Total = sum scores of each of the 4 quadrants

*Weinberg et al., Am Rev Respir Dis. 1984 ; 130 : 791.*

**Appendix II : Bronchoalveolar lavage**

1. **Sample**

Patient sedated - paralyzed - positive end expiratory pressure = 0 - FiO2 = 1

Endotracheal aspiration performed before the bronchoscopy – avoid lidocaine flush through the channel of the fiberscope – avoid aspiration of bronchial secretions through the suction channel - injection of room temperature sterile 0.9% saline – BAL performed in the pulmonary segment corresponding to the territory indicated radiologically. In the case of bilateral breach, the BAL will be carried out where purulent secretions are sitting, or if they do not exist in the lower lobes.

- The BAL is achieved with 3 fractions of 40 cc, with aspiration after each instillation. - The first fraction is analyzed separately. It is used only for the research of Legionella, Mycobacteria and fungal infections.

- The other 2 fractions are grouped together in a sterile container and sent to the laboratory (container type propylene, on which cells do not adhere).

**2) Analysis of the sample**

**Methods :** -2 polyvitex chocolate agar bacitracin-1 Sabouraud chloramphenicol agar blood agar plates (box)-1 agar Sabouraud chloramphenicol (tube)

- tubes of distilled water of 10 ml

- Mucomyst (N-acetyl cysteine), diluted to 1/10

- Pasteur pipettes

**reviews made :** - GRAM stain - counting the total number of cells - formula cell GIEMSA staining, established on 300 to 400 elements - search optional for viral or according to the clinical orientation cytopathic effect - inclusion culture: identification and susceptibility testing

- **Direct exam:** From the washing liquid, prepare two samples with the cytospin.
- 1 - Color with reagents of Diff-Quick (2 to 3 drops for filing): acknowledgement of the number of polymorphonuclear leukocytes (classified as: rare; many; very many), and also the presence of ciliated cells, macrophages and cells not identified in bacteriology.
- 2 - the second by Gram stain of color: observing the presence of bacteria.
- **culture**

Centrifuge 10 ml of BAL 10 mn at 4000 RPM. Decant the supernatant so that it remains about 0.5 ml of base add 0.5 ml of diluted Mucomyst 1/10 and shake the Vortex with this dilution, streak the Sabouraud in the tube for the research of Aspergillus and a blood agar for research of Pneumococcus (plater 2 drops) from the previous dilution to make a 1: 100 dilution, 2 drops in 10 ml sterile distilled water. Put 2 drops of this dilution and spread out on each of the media (blood agar and chocolate agar, Sabouraud agar). Put the blood and chocolate agar under CO2 and 37 ° C; the Sabourauds were incubated at 30 ° C.

- results

After 24 and 48 hours, look at the plates, quantify and identify each species. 1 colony "dilute" agar: 1.103 /ml

- interpretation

- Positive threshold : 104 CFU/ml

